### Sample size

The sample size calculation is based on a previously conducted pilot study among depressive patients suffering from insomnia [24]. In this pilot study, the mean PHQ-9 score was 11.5 in the intervention condition (I-Sleep + usual care) and 15.0 in the control condition (usual care alone) at three months of follow-up. Assuming an SD of 7.1, an alpha of 0.05, and a power of 0.80, this results in a total required sample of 130. With four participating mental healthcare outpatient clinics for mood disorders and an Intraclass Correlation Coefficient (ICC) of 0.05, the total required sample size for the current trial is 140. Considering a dropout rate of 20% based on the pilot study, the required sample size is 175. This means all four mental healthcare outpatient clinics for mood disorders ought to include approximately 44 patients in total, i.e., 22 patients per year.

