**Methods /design:**

This is a multi-centre RCT with measurements at baseline and at 3, 6, 9, and 12 months of follow-up. Patients with depression and an ID are randomised to either I-Sleep treatment followed by regular depression care or to regular depression care alone. Our aim is to recruit one hundred and seventy-five patients from multiple outpatient clinics for mood disorders. The primary outcome is the change in depressive symptoms over 12 months of follow-up measured with the Patient Health Questionnaire (PHQ-9). Secondary outcomes are recovery from depression (PHQ-9), insomnia severity (Insomnia Severity Index, ISI), daily functioning (Work and Social Adjustment Scale, WSAS), general quality of life (EuroQol 5-level version, EQ-5D-5L), and societal costs (Adapted versions of the iMTA Productivity Cost Questionnaire, iPCQ and iMTA Medical Cost Questionnaire, iMCQ).

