### Primary outcome measures

To assess the difference in the improvement in depression symptom severity as assessed by the PHQ-9 over time between the I-Sleep group and usual care group, linear mixed models that account for the repeated measures within patients will be used. Three hierarchical levels will be included in the linear mixed models: mental healthcare outpatient clinic for mood disorders, patient and time. The primary effect is described by the coefficient of the time-treatment interaction term. If necessary, the analysis will be adjusted for confounders and/or stratified for effect modifiers.

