Equally important, this RCT is based on a non-randomised pilot study within one outpatient mental healthcare clinic for mood disorders in which I-Sleep for depression proved to be effective. However, the findings also showed room for improvement in the applicability of I-Sleep in clinical practice. The ‘I-Sleep for depression protocol’ for this RCT was adapted based on the results of this pilot study to facilitate implementation in clinical practice and to reduce the drop-out rate of participants. The following adjustments were made. First, during the pilot study I-Sleep was offered simultaneously with usual care, but this was too much of a burden for the participants. I-Sleep is now offered as part of the depression treatment; the treatment starts with I-Sleep and, after completing the I-Sleep program, treatment continues according to the care-as-usual principle if necessary. We believe that this adjustment will procure a higher percentage of participants finishing the entire I-Sleep program. Secondly, during this RCT I-Sleep is preferably given by the same clinician as the subsequent usual depression treatment. Lastly, we have chosen to offer I-Sleep as a guided intervention instead of entirely as a self-help module. This may increase the acceptance and effectiveness of the treatment offered in people with depression [42].

Besides, many of the available studies on the effect of I-Sleep on insomnia have been conducted in the general population or in general practice patients with sleep problems. We are conducting research with I-Sleep in clinical practice among a population that is not yet well studied but experiences a huge suffering due to (clinically diagnosed) insomnia and depression. Which means that we will soon be able to present results that are relevant and generalizable to clinical practice, where the patients with these problems are found.

Needless to say, as in all studies, the scope of our design is limited. Within the current study design, we recruit patients from institutions that voluntarily applied for participation or with which good contacts already existed. This may cause a selection and/or convenience bias. It may be that these institutions are (more than others) already focused on treating patients with depression for insomnia-related symptoms as well. The contrast between the experimental condition and care as usual could therefore be smaller, which could lead to overly conservative estimates of the effect of I-Sleep.

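### The stated 80% power belongs to a single-visit difference at 3 months, not to the 12-month time-by-treatment interaction that is the primary test

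*Protocol article*

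**What the plan says.** The Sample size section of the protocol article takes its planning difference from the pilot: a mean PHQ-9 of 11.5 with I-Sleep added, against "15.0 in the control condition (usual care alone) at three months of follow-up". It continues: "Assuming an SD of 7.1, an alpha of 0.05, and a power of 0.80, this results in a total required sample of 130". Clustering by clinic brings this to 140 ("an Intraclass Correlation Coefficient (ICC) of 0.05, the total required sample size for the current trial is 140"), and dropout to 175 ("Considering a dropout rate of 20% based on the pilot study, the required sample size is 175").

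The abstract sets a longer horizon: "The primary outcome is the change in depressive symptoms over 12 months of follow-up". The PHQ-9 is measured at 0, 3, 6, 9 and 12 months. Under Primary outcome measures, the analysis is a linear mixed model with levels for clinic, patient and time, and "The primary effect is described by the coefficient of the time-treatment interaction term".

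On the pilot, the Background says that it was not randomised and gives a standardised difference in depressive symptoms of 0.55 (p = 0.19). The Discussion says that "during the pilot study I-Sleep was offered simultaneously with usual care", that in this trial I-Sleep comes first and usual care follows, and that delivery is now guided rather than wholly self-help.

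**The concern.** A power statement describes one test. Here the calculation uses two means at one visit, while the confirmatory test uses a model coefficient built from five visits over a year. The Sample size section gives no 12-month difference, no slope, no within-patient correlation and no coding of time. A reader therefore cannot tell what effect the primary test could detect.

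This matters because the interaction depends on the shape of the treatment difference over time as well as its size at 3 months. The trial could see exactly the 3.5 points it planned for at 3 months and still have anything from very high to negligible power on its primary test. A reader who takes the 80% at face value would credit that test with a sensitivity that nobody has worked out.

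The source of the 3.5 points adds to the uncertainty. It comes from a non-randomised pilot with a different sequence and format of delivery.

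**Working it through.** **1. Reproducing the plan's figure.** Inputs from the Sample size section: difference 15.0 − 11.5 = 3.5, SD 7.1, alpha 0.05, power 0.80. Sidedness is not stated. For two means, n per arm = 2 × SD² × (1.96 + 0.84)² / difference² = 2 × 50.41 × 7.85 / 12.25 = 64.6, so 65 per arm and **130 in total**, as stated. A one-sided test would give 102. The 80% is therefore that of a two-sided two-sample comparison at one visit. Dropout: 140 / 0.80 = 175, as stated. The step from 130 to 140 is a separate matter, and 140 is taken as given below. With 70 per arm, the same 3-month comparison has 83% power.

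**2. Assumptions for the interaction.** There are 70 evaluable patients per arm, and SD 7.1 at every visit. The within-patient correlation r is 0.4–0.7 with compound symmetry and no random slope. None of the correlation structure is in the article. A random slope would lower the power figures. The clinic level is ignored, since randomisation is by patient and stratified by clinic.

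**3. Linear time.** Visits are scored −2, −1, 0, 1, 2 (sum of squares 10).

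- Standard error of the slope difference per 3 months = √[2 × 50.41 × (1 − r) / (10 × 70)] = 0.294 at r = 0.4 and 0.208 at r = 0.7.
- Slope difference = Σ(score × difference at that visit) / 10.
- Power is approximately Φ(slope / SE − 1.96), plus the small opposite tail.

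| Difference at 0, 3, 6, 9, 12 months | Slope per 3 months | Power, r = 0.4 to 0.7 |
|---|---|---|
| 0, 0.875, 1.75, 2.625, 3.5 (grows steadily) | 0.875 | 85–99% |
| 0, 3.5, 3.5, 3.5, 3.5 (held) | (−3.5 + 3.5 + 7) / 10 = 0.70 | 66–92% |
| 0, 3.5, 2.92, 2.33, 1.75 (fades to half) | (−3.5 + 2.33 + 3.5) / 10 = 0.233 | 12–20% |
| 0, 3.5, 2.625, 1.75, 0.875 (fades to a quarter) | (−3.5 + 1.75 + 1.75) / 10 = 0 | 5% (error rate) |

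In the last row I-Sleep is better at every follow-up visit, yet the slope difference is zero. If the difference fades further, the slope changes sign, and a rejection would then mostly favour the control arm.

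The detectable 12-month difference at 80% power, along a straight line, is 4 × 2.80 × SE. This is 4 × 2.80 × 0.294 = 3.3 points at r = 0.4 and 4 × 2.80 × 0.208 = 2.3 points at r = 0.7.

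**4. Categorical time, 12-month interaction (change from baseline).** SE = √[(2/70) × 2 × 50.41 × (1 − r)] = 1.31 at r = 0.4 and 0.93 at r = 0.7.

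- If 3.5 remains at 12 months, power is 76–96% (83% at r = 0.5, where the variance equals that of the two-sample comparison).
- If 1.75 remains, power is 26–47%.
- The detectable difference is 2.80 × SE = 3.7 to 2.6 points.

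**5. A contrast that the plan does not test.** For the baseline-adjusted mean difference over the four follow-up visits, SE = √[(2/70) × 50.41 × ((1 + 3r)/4 − r²)] = 0.750 at r = 0.4 and 0.641 at r = 0.7. The detectable difference is 2.80 × SE = 2.1 to 1.8 points.

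**The case against.** The strongest reply is that sizing on a single visit is usually conservative for a repeated-measures analysis. Part of this stands. If time is categorical, 3.5 points persist to 12 months and the correlation is 0.5, the interaction has the same variance as the two-sample comparison and 83% power. If the difference builds steadily to 3.5, even the linear-time test has at least 85%. The interaction figures also depend on trajectories and correlations that the article does not supply, and it does not say how time is coded. But the reply holds only under persistence or growth, which the Sample size section does not state. A held effect with linear time gives less than 80% at the lower correlations.

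A reader might infer that the trial is underpowered. The documents do not support that, because they give no 12-month effect and several plausible cases exceed 80%.

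A reader might also infer that the pilot figure is too optimistic, because usual care now starts after I-Sleep. That is not supported either. The article does not say how much usual care patients had received by 3 months in either study, and antidepressants are allowed in both arms. Delivery also became guided, and the sequence was changed to improve completion. The net direction is unknown.

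Nor would a null result be unreadable, since its estimate and confidence interval would still inform. It could also be said that the analysis plan may settle the matter. It may do so for the model, but the power claim is made in this article and belongs to a different contrast.

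**Conclusion.** The point holds as a mismatch between the powered contrast and the tested one. The 130 reproduces exactly as a two-sample comparison at 3 months, and the article gives no basis for transferring the 80% to the 12-month interaction. Given 3.5 points at 3 months, power for a linear-time interaction runs from the 5% error rate (fading to 0.875) to 92% (held, correlation 0.7). If the difference instead grows steadily to 3.5 by 12 months, power reaches 99%. The categorical version runs from 26% to 96% over the two cases examined. All of this rests on 140 evaluable patients, a constant SD of 7.1 and an assumed correlation of 0.4–0.7. The conclusion is that power for the primary test is unstated, not that it is low. Whether the pilot's 3.5 points will recur is uncertain in either direction.

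**What to change.** Keep 175 and revise the Sample size paragraph:

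- Label the 80% as applying to the 3-month difference only.
- State power for the interaction named under Primary outcome measures, with the coding of time, a within-patient correlation range and the difference detectable at 80% power. Under the assumptions above, this is about 2.3–3.3 points at 12 months for a linear slope, or 2.6–3.7 points for a categorical 12-month interaction.
- Quote 1.8–2.1 points only if the primary contrast is itself changed to the baseline-adjusted mean difference over the four follow-up visits. Otherwise the paragraph would again describe a test that is not primary.
- Note that the pilot's 3.5 points came from non-randomised, concurrent, self-help delivery, so its transfer to this trial is uncertain.

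The cost is a short recalculation and some text, with no change to recruitment. The drawback is that the stated power may look less favourable than 80%.

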### Statistical analysis

Statistical analyses will be performed according to the intention-to-treat principle and will include a head-to-head comparison of the intervention group with the usual care group. A priori, we decided on a subgroup analysis stratified for the use of sleep medication at baseline. Analyses will be (partly) conducted by two independent researchers to check the validity and correctness of the analyses and it will be documented which software is used over the course of this project.

### Primary outcome measures

To assess the difference in the improvement in depression symptom severity as assessed by the PHQ-9 over time between the I-Sleep group and usual care group, linear mixed models that account for the repeated measures within patients will be used. Three hierarchical levels will be included in the linear mixed models: mental healthcare outpatient clinic for mood disorders, patient and time. The primary effect is described by the coefficient of the time-treatment interaction term. If necessary, the analysis will be adjusted for confounders and/or stratified for effect modifiers.

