### The investigational treatment: I-Sleep, CBT-I for insomnia

I-Sleep is a guided, internet-based treatment based on CBTi [22, 27, 28]. The I-Sleep program consists of five online sessions comprising text, videos, and exercises. Feedback on the exercises is provided by a trained therapist through the secured online platform. Online sessions are divided by subject addressing: 1) psychoeducation on normal sleep, sleep disorders, and sleep hygiene (i.e., behaviours that can promote or impede sleep), 2) sleep restriction (i.e., restricting time in bed to increase sleep pressure) and stimulus control (i.e., reinforcing the association of the bed with sleeping), 3) rumination and relaxation techniques, 4) cognitive restructuring (i.e., changing common misconceptions about sleep) and 5) relapse prevention. Patients need to monitor their sleep by filling out a sleep diary throughout the intervention and complete the exercises in the digital workbook. The therapy program takes less than 30 min a day. The total duration of the insomnia intervention is five weeks.

The intervention is provided in a blended format, comprising both face-to-face or videoconferencing sessions and online sessions. To promote compliance and establish a positive working relationship between the patient and therapist the first face-to-face (f-t-f) session is scheduled prior to the first online session. A second f-t-f session is scheduled after the second online session to provide additional support during sleep restrictions The third and final f-t-f session is scheduled upon completion of all online sessions. Following the I-Sleep intervention, all participants allocated to the intervention group will receive usual care for depression. Preferably both I-Sleep and the usual depression treatment will be delivered by the same therapist so that cognitive techniques introduced during I-Sleep may be worked through more quickly during depression treatment. However, this is not mandated by the study protocol.

I-Sleep is delivered through a secure web-based online treatment platform (Minddistrict, www.minddistrict.com). The platform is owned by a commercial stakeholder from which specialized mental healthcare outpatient clinics for mood disorders buy services. The internet platforms include a PC interface and mobile application providing patients access to I-Sleep, a digital workbook and a secure communication channel for both the therapists and patients.

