### Usual care

All patients in this study will receive usual care for depression. Usual care is given according to the multidisciplinary Dutch guideline for depression care and contains (group) psychotherapy and/or antidepressant medication treatment. Therapy and medication use during the trial is monitored. Furthermore, therapists are requested to refrain from CBTi (particularly I-Sleep), but usual care is not restricted in any other way.

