### Secondary outcome measures

To assess the difference in recovery from depression between the I-Sleep and usual care groups over a period of 12 months after baseline, logistic mixed models will be used to account for repeated measurements within patients. To assess the difference in the improvements in insomnia symptom severity, daily functioning, and quality of life over time between the I-Sleep and usual care groups, linear mixed models will be used to account for repeated measurements within patients. Three hierarchical levels will be included in the logistic and linear mixed models: mental healthcare outpatient clinic for mood disorders, patient and time. The primary effect is described by the coefficient of the time-treatment interaction term. If necessary, the analysis will be adjusted for confounders and/or stratified for effect modifiers.

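### The mixed models omit the therapist although I-Sleep is therapist-delivered in one arm only; unless therapists act alike in both arms, the standard error is likely somewhat too small

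*Protocol article*

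**What the plan says.** Under Primary outcome measures: "Three hierarchical levels will be included in the linear mixed models: mental healthcare outpatient clinic for mood disorders, patient and time". Under Secondary outcome measures: "Three hierarchical levels will be included in the logistic and linear mixed models: mental healthcare outpatient clinic for mood disorders, patient and time". In both, the effect of interest is the time-treatment coefficient.

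The section on the investigational treatment describes five online sessions with feedback from a trained therapist, plus three sessions in person or by video. It adds: "Preferably both I-Sleep and the usual depression treatment will be delivered by the same therapist", though this is not mandated. Usual care "contains (group) psychotherapy and/or antidepressant medication treatment", and therapists are asked not to give CBTi within it.

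Randomisation is by patient and stratified by clinic. The Sample size section allows for clustering by clinic only (ICC 0.05, four clinics). The article does not say how many therapists take part, how many patients each treats, or whether a therapist treats one arm or both.

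**The concern.** A list of three named levels excludes a fourth, so this is a stated modelling choice and not a detail left to an analysis plan. Patients who share an I-Sleep therapist share that therapist's skill in running the sessions and giving feedback, so their improvement may be correlated. Patients in the same usual-care therapy group may be correlated for a similar reason.

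The clinic level does not cover this. Stratified randomisation largely balances a common clinic effect between the arms. Variation between therapists in how well they deliver I-Sleep has no counterpart among controls, so it does not cancel from the comparison. A model that treats patients of one therapist as independent then understates the uncertainty of the I-Sleep arm. The confidence interval for the primary PHQ-9 effect is too narrow, and a true null is rejected more often than planned.

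**Working it through.** **Inputs from the Sample size section.** "the mean PHQ-9 score was 11.5 in the intervention condition (I-Sleep + usual care) and 15.0 in the control condition" gives a difference of 3.5 points. "Assuming an SD of 7.1, an alpha of 0.05, and a power of 0.80, this results in a total required sample of 130". After the clinic allowance 140 are required, and after 20% dropout 175.

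**The plan's own figure.** Two-sided test: n per arm = 2 × 7.1² × (1.960 + 0.842)² / 3.5² = 64.6, rounded up to 65, total 130. This matches. 140 / 0.8 = 175 also matches. The step from 130 to 140 is taken as given here. With 70 analysed per arm and no therapist effect, SE = 7.1 × √(2/70) = 1.200, 3.5 / 1.200 = 2.916, and power = Φ(2.916 − 1.960) = 83%.

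**Assumptions, not in the article.** The therapist ICC (the share of variance in the tested outcome due to therapist) is 0.02 to 0.10. The number of analysed patients per I-Sleep therapist, m, is 3 to 8. For orientation, 16 I-Sleep therapists would mean m = 70/16 = 4.4 analysed, or 88/16 = 5.5 randomised.

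**Case A: clustering in the I-Sleep arm only.** Variance factor F = (1 + [1 + (m − 1) × ICC]) / 2. Type I error when the therapist is ignored = 2 × (1 − Φ(1.960/√F)). Power of a valid 5% test with 140 analysed = Φ(2.916/√F − 1.960).

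Example, ICC 0.05 and m = 4.4: F = (1 + 1.17)/2 = 1.085 and √F = 1.042. Then 1.960/1.042 = 1.882, so the type I error is 6.0%. Power = Φ(2.800 − 1.960) = 80%.

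| ICC | m | F | Type I error | Power, 140 analysed |
|---|---|---|---|---|
| 0.02 | 3 | 1.020 | 5.2% | 82% |
| 0.02 | 5.5 | 1.045 | 5.5% | 81% |
| 0.02 | 8 | 1.070 | 5.8% | 80% |
| 0.05 | 3 | 1.050 | 5.6% | 81% |
| 0.05 | 4.4 | 1.085 | 6.0% | 80% |
| 0.05 | 5.5 | 1.113 | 6.3% | 79% |
| 0.05 | 8 | 1.175 | 7.1% | 77% |
| 0.10 | 3 | 1.100 | 6.2% | 79% |
| 0.10 | 5.5 | 1.225 | 7.7% | 75% |
| 0.10 | 8 | 1.350 | 9.2% | 71% |

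At ICC 0.05 and m = 5.5 the true standard error is √1.113 = 1.055 times the reported one, so the interval is about 5% too narrow.

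**Case B: the same therapists treat both arms with equal effect.** The therapist effect cancels from the comparison and the variance factor is about 1 − ICC. There is no inflation. The formula gives 4.8% to 3.9% over ICC 0.02 to 0.10.

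**Simulation check.** One post-baseline score, 140 patients, four clinics, a clinic-adjusted test ignoring the therapist, 8,000 trials per setting. Case A at ICC 0.05 gave 5.3% (m = 3) and 6.1% (m = 6). At ICC 0.10 it gave 6.0% and 8.0%. Case B gave 4.6% to 5.2%.

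**Which effect is tested.** A second simulation had 176 patients, five visits, 16 I-Sleep therapists and within-patient correlation 0.5. It used clinic-adjusted patient-level summaries, with clustering in the I-Sleep arm. At ICC 0.05 (0.10), type I error was about 7% (9%) for mean post-baseline change and about 6% (7%) for a linear slope. Neither simulation fits the planned three-level model itself, so these results show direction and order of size only.

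**The case against.** The strongest reply is that therapists may well treat both arms. All therapists involved are trained before taking part, and the request to withhold I-Sleep from usual care matters most for therapists able to give it. I-Sleep therapists preferably also give the depression treatment, so they are ordinary clinic staff. The article never says that controls are treated by different therapists. A reader might infer that only trained therapists deliver I-Sleep while anyone may treat controls, but no section supports that. Nor does any section support figures that need separate therapists in each arm.

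This reply stands in part. It rules out claiming the error as a certainty. It does not remove the point, because treating both arms restores 5% only if each therapist's effect is the same in both. Differences in how well therapists deliver I-Sleep arise in one arm and remain outside the model even when therapists are shared.

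A second reply concerns power. A reader might infer that the planned 80% is lost. On 130 patients it would fall to about 78%, 76% and 74% at ICC 0.05 with 3, 5.5 and 8 patients per therapist. But the plan is for 140 analysed, and the figures are then 81%, 79% and 77%. This reply stands: at a moderate ICC the power is essentially delivered.

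A third is that a full therapist structure, partly nested and partly crossed, may not converge with four or five analysed patients per therapist, least of all in the logistic model. Patients on medication alone may have no psychotherapist to enter. This also stands, and it is why the remedy needs a fallback.

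**Conclusion.** The point holds in conditional form. The omission of the therapist is stated text. The understated standard error is likely, but it is not established, because it depends on how therapists relate to arms and on how much they differ in delivering I-Sleep.

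If clustering acts in the I-Sleep arm only, the size is modest: a type I error of about 6% in the middle of the assumed range, little above 5% at ICC 0.02, and about 9% at the upper end. If therapists treat both arms with equal effect, the test is correct or slightly conservative. It would go too far to conclude that the standard error is certainly wrong or that the stated alpha and power are certainly not achieved. What is supported is a likely modest error in alpha and interval width, from a source that the design makes plausible and the model leaves out. Power becomes a concern only towards ICC 0.10 (71% to 79%).

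**What to change.** - State whether therapists treat patients in one arm or both.
- Record for every patient the I-Sleep therapist and, where there is one, the depression therapist or therapy group.
- Add to the primary model a therapist random effect that acts on change after baseline, confined to the I-Sleep arm if the design is partially nested. A therapist intercept alone would hardly alter the standard error, because a constant therapist effect drops out of the time-treatment coefficient.
- Use Satterthwaite or Kenward-Roger degrees of freedom.
- Pre-specify a fallback if the model does not converge, and report the three-level model alongside.
- Say whether the term carries over to the secondary models, which share the omission.

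The cost is one identifier per patient, which the clinics should know, and a few lines of analysis text. No extra patients are needed. The article reports inclusion as ongoing, and the identifier is easiest to secure during that phase. The downside is a slightly wider interval and a therapist variance that will be estimated imprecisely.

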### Randomization, blinding and treatment allocation

After inclusion, participants are randomly assigned to either the intervention group I-Sleep (before the start of the usual care) or the control group (usual care alone) on a 1:1 ratio. Variable block sizes are used. Randomization takes place at the patient level and is stratified by mental health outpatient clinics for mood disorders. An independent researcher has created an allocation scheme using a computerized random number generator (Castor). Randomization will be performed by another independent research assistant who reveals the randomization outcome. Due to the nature of the intervention, blinding of patients, therapists, researchers and research assistants was not possible.

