### Primary outcome: depression severity

The primary outcome is the change in depressive symptoms during one year of follow-up. Depressive symptoms will be assessed with the web-based Patient Health Questionnaire-9 (PHQ-9) at baseline and at 3, 6, 9 and 12 months of follow-up. The PHQ-9 scores each of the nine DSM criteria on a scale from "0" (not at all) to "3" (nearly every day), resulting in a total score ranging between 0 and 27 which is divided into increasing severity categories resulting in the PHQ Depression Severity Index [29]. Recent studies show that the PHQ-9 delivered using web-based technology is a reliable instrument to assess the severity and frequency of depressive symptoms in the previous two-week period [30, 31]

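### The primary time-treatment interaction is set up without a prespecified adjustment for baseline PHQ-9 and, under the usual specification, gives up some precision

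*Protocol article*

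**What the plan says.** The section on the primary outcome defines it as a change: "The primary outcome is the change in depressive symptoms during one year of follow-up". Measurement is at five time points: "Depressive symptoms will be assessed with the web-based Patient Health Questionnaire-9 (PHQ-9) at baseline and at 3, 6, 9 and 12 months of follow-up".

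Under Primary outcome measures, the analysis compares improvement over time between arms: "linear mixed models that account for the repeated measures within patients will be used", with clinic, patient and time as the three levels. The effect parameter and the only provision for covariates, which is conditional, are then given together: "The primary effect is described by the coefficient of the time-treatment interaction term. If necessary, the analysis will be adjusted for confounders and/or stratified for" variables that modify the effect. Baseline PHQ-9 is not named as a covariate, and no common baseline mean for the two arms is mentioned. Secondary outcome measures repeats this scheme for the continuous outcomes: "To assess the difference in the improvements in insomnia symptom severity, daily functioning, and quality of life over time between the I-Sleep and usual care" arms.

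Two further statements bear on the remedy. The section on randomization says "Randomization takes place at the patient level and is stratified by mental health outpatient clinics for mood disorders", and adds that patients could not be blinded. The Recruitment section has participants randomised first and then sent the link to the baseline questionnaire.

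**The concern.** Comparing improvement from T0 through an interaction normally means that T0 is one of the outcome rows and that the arms may differ freely there. The interaction then subtracts the whole chance difference between arms at T0. That treats baseline as if it predicted follow-up with a slope of exactly 1. When the true slope is smaller, the subtraction adds noise, and an analysis that estimates the slope is more precise.

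The conditional clause does not supply this adjustment. It speaks of confounders, to be added if the data seem to call for them. In a randomised comparison, baseline PHQ-9 earns its place because it is prognostic, and that is known before any data are seen. Leaving it to a later judgement also leaves open an analytic choice on the primary outcome.

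At stake is precision on PHQ-9 and, by the same wording, on insomnia severity, daily functioning and quality of life.

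**Working it through.** **Inputs from the Sample size section.** PHQ-9 means of 15.0 and 11.5 at three months, so a difference of 3.5; SD 7.1; alpha 0.05; power 0.80; totals of 130, then 140 with the intraclass correlation, then 175 with 20% dropout. Allocation is 1:1, so 140 evaluable patients means 70 per arm.

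**Assumptions, because the article gives no figure.** The correlation rho between baseline and follow-up PHQ-9 (range 0.3 to 0.7), and the SD at T0 (7.1 as at follow-up, or narrower). No clustering term is added.

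**The plan's own figure.** n per arm = 2 × (7.1/3.5)² × (1.96 + 0.84)² ≈ 64.6, rounded up to 65, total 130. This reproduces with a two-sided alpha. The dropout step also reproduces: 140/0.80 = 175. With 70 per arm, comparing follow-up scores alone has SE = 7.1 × √(2/70) = 1.20 and power 83%.

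**Single-visit contrast, SD 7.1 at both times.**
- Change score: SE = 7.1 × √(2 × 2(1 − rho)/70)
- Baseline-adjusted: SE = 7.1 × √(2(1 − rho²)/70)
- Power = Φ(3.5/SE − 1.96); variance ratio, adjusted to change, = (1 + rho)/2

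| rho | SE change | SE adjusted | Variance ratio | Power change | Power adjusted |
|---|---|---|---|---|---|
| 0.3 | 1.420 | 1.145 | 0.65 | 69% | 86% |
| 0.5 | 1.200 | 1.039 | 0.75 | 83% | 92% |
| 0.7 | 0.930 | 0.857 | 0.85 | 96% | 98% |

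A generalised least squares calculation with five visits, categorical time, equal correlation between visits and a free treatment effect at T0 gives exactly the change-score SEs. Removing the treatment effect at T0 gives the adjusted SEs.

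**Linear time.** The coefficient is now a slope difference. With equal correlation between visits and an effect reaching 3.5 at 12 months, power with a free against a common baseline is 79% against 94% at rho 0.3, 90% against 96% at 0.5, and 99% against 99.5% at 0.7. The variance ratios are 0.61, 0.75 and 0.86.

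**Narrower spread at T0.** With a T0 SD of 5.0 the change-score variance is 7.1² + 5.0² − 2 × rho × 7.1 × 5.0. The adjusted variance is unchanged.
- rho 0.3: variance 54.11, SE 1.243, power 80% against 86%, a gain of about 6 points.
- rho 0.5: variance 39.91, SE 1.068, power 91% against 92%, a gain of about 1 point.
- rho 0.7: the slope of follow-up on baseline is 0.7 × 7.1/5.0 = 0.99, so the two analyses coincide.

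**The case against.** The strongest reply is that the article is silent where this point assumes an answer. It does not state the time coding, whether a treatment main effect is included, or expressly that T0 is an outcome row. A model without a treatment effect at T0 would fit the text and would already be adjusted for baseline. Such detail is often left to the analysis plan. This stands in part: one cannot say that the trial will run an unadjusted analysis. But the article does fix the effect parameter and the rule for covariates, and that rule makes baseline adjustment conditional on the wrong criterion.

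A second reply is that the size is fragile. All patients have diagnosed major depression at entry, so a narrower spread at T0 is plausible, and the gain then falls to a few points or none. This stands, and the range is shown above.

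A third reply is that baseline adjustment assumes T0 is unaffected by allocation, which the order of randomisation and T0 does not secure. If knowing the allocation shifted T0 answers only temporarily, the change score carries the full shift and the adjusted contrast only about rho times it (with equal SDs). If it caused selective completion of T0 and hence a lasting difference between arms, the change score removes that difference, while adjustment leaves about (1 − rho) of it. This stands and shapes the fix.

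A reader might infer that the planned analysis is biased or that the trial is underpowered. The documents support neither. With T0 unaffected by allocation, the interaction is unbiased across randomisations. Power below 80% arises only in some assumed cases: at rho 0.5 or above, with equal SDs and equal correlation between visits, it is at least 83%.

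**Conclusion.** The point holds as one of efficiency. Under the usual specification, the interaction named as the primary effect is a change-score type of contrast, never more precise than one adjusted for baseline PHQ-9 and usually less so. The conditional clause on confounders does not guarantee the adjustment.

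With equal SDs at T0 and follow-up, the single-visit gain runs from 17 percentage points of power at rho 0.3, through 9 at 0.5, to 2 at 0.7. With a T0 SD of 5.0 it is about 6, 1 and 0. Neither rho nor the T0 SD is in the article, so no single value can be claimed. The adequacy of the planned 175 patients is not decided by this point.

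**What to change.** In Primary outcome measures, and for the continuous outcomes in Secondary outcome measures, state outside the conditional clause that the model always adjusts for the baseline value of the outcome. The preferred form takes T1 to T4 as outcomes, includes baseline and its interaction with visit as covariates, reads the effect from treatment contrasts at T1 to T4, and keeps clinic in the model. This also settles the time coding.

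The alternative, T0 to T4 as outcomes with a common baseline mean for both arms, should be used only if T0 is completed before the patient knows the allocation.

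The cost is a sentence or two of analysis wording before database lock, with no new data and no more patients. Two small burdens follow: patients without a T0 score need a simple baseline imputation, and a change-score sensitivity analysis should be reported in case knowledge of allocation led to selective completion of T0.
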